#### Data collection

Figure 3 depicts the data collection timeline. Data collection was conducted at two-time points for students—before the intervention commences and after the intervention period. At pre-intervention, demographic information, such as age and gender, and the baseline behaviours and psychosocial factors were collected from students using a questionnaire (“Main questionnaire”). At post-intervention, students completed the post-intervention main questionnaire (consisting of the same questions as in pre-intervention) and a short feedback survey and were invited to participate in an FGD. Teachers also completed a feedback survey after delivering each lesson. All data collected were delinked from their personal information and replaced with a unique code.

**Fig. 3 Fig3:**
[figure not shown]
Data collection timeline in Phase 2 and Phase 3

##### Main questionnaire

This questionnaire consisted of questions to assess student’s knowledge; ideation factors (attitudes, perceived norms, self-efficacy, social support); and environment related to healthy eating and physical activity. These questions were adapted from validated questionnaires [48, 49]. Behavioural outcomes, such as intentions, habit strength, fruit and vegetable intakes, and physical activity and sedentary time spent, were also captured using the main questionnaire. Details on behavioural outcomes questions are described in the next section.

##### Feedback surveys

Student’s feedback survey consisted of questions on their acceptance (e.g. “I like this style of health education lessons.”) and satisfaction (e.g. “I understood what was taught in the lessons.”, “The lessons have made me more interested to eat healthily and be physically active.”) of the intervention. Teacher’s feedback surveys consisted of a checklist of activities implemented during the lesson, their satisfaction with the instructions provided in the teacher’s guide, their acceptance of facilitating this interactive format of health education lesson, etc.

##### Focus group discussions (FGD)

Two groups of four to six students who participated in the intervention and a group of at least six teachers who delivered the intervention were selected to participate in the FGD from each school. Semi-structured topic guides were used in the FGDs, which included questions to explore healthy eating and physical activity ideation among students and in-depth feedback on the intervention implementation. The topic guide for FGDs with students focused more on exploring ideation, while FGDs with teachers focused more on the implementation.

#### Data analysis

Descriptive statistics were tabulated using frequencies, means, and standard deviations from the quantitative data (e.g. recruitment and participation rates, acceptability and satisfaction rates, online questionnaires) separately for pre-intervention and post-intervention data. Responses from the main questionnaire were examined for ceiling effect. Qualitative data from FGDs were transcribed and analysed using applied thematic analysis, both inductively and deductively [50], to explore the implementation of components A and B and ideation.

The findings and feedback from this phase informed the refinement of the intervention for Phase 3, including extending the intervention period, having more interactive time in class, rephrasing some questions for clarity, and modifying the response options of diet and movement outcomes to capture these behaviours with minimal ceiling effects better. Reported results from Phase 2 will be published separately.

### Phase 3: Pilot testing of the whole PEDAL intervention

#### Objectives

A pilot study was conducted in Phase 3 to assess the feasibility of the whole PEDAL intervention (components A to D) and explore the potential effectiveness to inform the planning for a future large-scale definitive trial. A concurrent mixed methods quasi-experimental study design was used for this pilot study. Figure 4 illustrates the enrolment, intervention components, and assessment schedule for Phase 3.

**Fig. 4 Fig4:**
[figure not shown]
Schedule of enrolment, interventions, and assessments of the pilot study

#### Key measures

##### Feasibility

Similar to Phase 2, the five feasibility dimensions were assessed with the addition of a sixth dimension, potential effectiveness, which examines if there is preliminary evidence that the intervention has the potential to bring about positive behaviour change. Changes in behavioural outcomes will also be explored to inform the decision-making of the primary outcome and power calculation for a subsequent larger definitive trial. Additionally, FGDs will be conducted with students and teachers to explore any perceived behaviour improvements among the students. With the addition of components C and D, additional measures were also collected from canteen vendors and parents and on the class and canteen environments. Details of the feasibility dimensions and the progression criteria to the next phase (future definitive trial) are described in Table 3.

##### Behavioural outcomes

Diet and movement behaviours: Key dietary behaviours to be assessed include fruit and vegetable intakes (in servings per day), while movement behaviours will include time spent on sedentary activities and physical activities (in minutes per day). Students will be asked to report, via a questionnaire, their frequency and usual portion size of their fruit and vegetable intakes in the past week, as well as the time spent on moderate-to-vigorous physical activity (MVPA) and sedentary activities (using screen time as a proxy) in the past week. In addition, students will also complete a 3-day activity record on a web-based application (MEDAL), which was developed by the research team [13] and previously validated against self-reported intakes of school meals [51] and wrist-worn accelerometers [52], to complement the data obtained from the questionnaire.Behavioural intentions: Five items will be used to assess students’ intentions to meet the daily recommended guidelines for fruit intake, vegetable intake, physical activity, and spending less time on sedentary activities in the next three months. A 5-point Likert scale (1, not true for me at all to 5, very true of me) will be used to assess these questions.Habit strength: To assess change in the behavioural habits among students, four items will be used to measure the habit strength in each lifestyle behaviour (i.e. fruit intake, vegetable intake, physical activity, sedentary behaviour). The questions will be adapted from past validated questionnaires [53, 54].Health-related quality of life: In Phase 3, the study will also assess changes in children’s health-related quality of life as previous research has shown that improvements in diet and physical activity levels can contribute to improvements in health-related quality of life in children (HRQoL) (63, 64). As this intervention aims to change children’s lifestyle behaviours, we are interested in examining whether the intervention affects children’s HRQoL. KINDL-Kid (65, 66), which comprised 24 items and six subscales (physical health, general health, family functioning, self-esteem, social function, and school functioning), will be used to measure HRQoL in this study.

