#### Component A: Interactive health education lessons

Consisting of five interactive face-to-face lessons, the PEDAL health education lessons were developed to cover topics on healthy eating, reducing sedentary behaviours, and habit formation (see link for introductory video: https://bit.ly/pedal-intro, and Table 2 for a summary of lesson topic and content). The concept of habit formation was included as increasing evidence has demonstrated that habit is a more important predictor of a behaviour (e.g. fruit and vegetable consumption) than intentions [33, 34] and the need to identify contingency plans that help support existing habits [35]. Adapting the concept from a habit-based healthy feeding intervention [36], students were taught to incorporate strategies such as goal setting, self-monitoring (through understanding triggers and circumstances), and self-efficacy in the PEDAL lessons. To help facilitate students’ goal setting, which provides a starting point for making specific behavioural changes, students received feedback on their lifestyle behaviours based on their baseline lifestyle behaviour data collected. To reduce sedentary time, health education lessons, typically conducted with seated students, were modified to incorporate standing and movement activities during lessons to break up sitting time [37]. This approach has the triple benefits of reducing students’ sitting time, teaching them the concept of reducing sedentary behaviour as well as being more interactive, to better engage the students and change their perception of health education lessons.

**Table 2 Tab2:** Topics covered in the health education lessons

Lesson	Topic	Content and activities
1	Calorie balance and nutrient density	• Educational video on energy density and portion sizes; • Interactive and active stand-up game to reinforce concepts learnt and bust diet myths Video links: https://bit.ly/pedal-caloriebalance, https://bit.ly/pedal-nutrientdensity (See Additional File 2 for snapshots of the lesson videos)
2	Habit formation	• Educational video on the habit formation concept; • Worksheets on goal setting based on class and individual feedback on diet and lifestyle; • Worksheets on setting action plans for diet and movement. Video link: https://bit.ly/pedal-habitformation (See Additional File 2 for snapshots of the lesson video)

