Practicality	Can the intervention be implemented with available resources, time, training, and materials?	• Post-intervention FGDs with students and teachers • Post-intervention interviews with canteen vendors^a^ • Number of parent volunteers participated in canteen activities^a^	• Good feedback on the resources provided • Low level of perceived barriers on implementation from teachers and canteen vendors^a^ • At least 5 parent volunteers participated in the canteen activities^a^
Implementation	Are teachers able to implement the intervention with fidelity (as intended by the research team)? Are the canteen posters still in place by the end of the intervention?^a^	• Teacher-reported implementation checklist • Class observations^a^ • Canteen environmental scans^a^	• ≥ 75% fidelity among teachers, based on the checklist • ≥ 75% fidelity among teachers, based on class observations^a^ • ≥ 75% of the posters are still in place at the end of the intervention^a^
Potential Effectiveness of the whole PEDAL intervention^a^	Is there preliminary evidence of potential for bringing about positive change? What influenced the change (or no change) among the students?^a^	• Student outcome data^a^ • Canteen environmental scans ^a^ • Post-intervention interviews with students and teachers^a^ • Post-intervention interviews with canteen vendors^a^	• Improvements in fruit and vegetable intakes^a^ • Improvements in MVPA min/day^a^ • Reduction in screen time min/day^a^ • Improvements in ideation factors^a^ • Improvements in student’s health-related quality of life^a^ • Perceived improvements in behaviour and increased motivation for behaviour change^a^

^a^Additional items measured in Phase 3

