#### Data collection

The data collection timeline for this phase is illustrated in Fig. 3. Data collection for Phase 3 was similar to Phase 2 with the addition of a mid-intervention, a 6-month post-intervention data collection, and additional measures collected from parents and canteen vendors.

The instruments used for quantitative measurements in Phase 3 were largely similar to those used in Phase 2, with some refinements made to the phrasing and response options in the main questionnaire. A feedback survey for parents was also developed to assess parent’s feedback on the lesson videos and home activities. An observation checklist of the canteen environment was also developed to examine the availability of healthier choices, the canteen vendor’s compliance with the Healthy Meals in School Programme guidelines [44], the interaction between canteen vendors and students, etc.

The selection of participants for the focus groups was the same as in Phase 2. Different semi-structured topic guides were developed for Phase 3 to assess the extent of students’ and teachers’ awareness and knowledge retained from the PEDAL lessons, collect feedback on the whole PEDAL intervention, and explore perspectives on behaviour change and habit formation in students. For the short interviews with canteen vendors, guiding questions were developed to explore their perspective of the school food environment and perceived changes among students after the intervention. All data collected were delinked from their personal information and replaced with a unique code.

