#### Data analysis

Descriptive statistics from the quantitative data for the recruitment capability, data collection procedures, and social validity dimensions will also be presented separately for pre-intervention and post-intervention data in this phase. Pre-post intervention comparisons of the behavioural outcomes will be assessed using appropriate statistical analyses (e.g. paired *t*-test for normally distributed variables and Wilcoxon signed rank test for variables with non-parametric distributions). Pre- and post-intervention ideation scores for healthy eating and physical activity, derived from the composite of the ideation variable scores, will be compared. Regression analyses will be conducted to examine the associations between ideation scores and behavioural outcomes.

Similar to Phase 2, qualitative data from FGDs and interviews will be transcribed and analysed using applied thematic analysis [50], to answer the research questions for the social validity, practicality, implementation, and (perceived) potential effectiveness dimensions. When possible, both quantitative and qualitative data will be integrated and reported for the feasibility evaluation.

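### Reported fruit and vegetable servings may shift without a change in eating, because students judge their own portion size and Lesson 1 teaches portion sizes between the two measurements

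*Protocol article*

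**What the plan says.** The Phase 3 section on behavioural outcomes gives fruit and vegetable intake in servings per day. The questionnaire asks students for "their frequency and usual portion size of their fruit and vegetable intakes in the past week", so one of the two inputs to servings is the student's own view of portion size. A 3-day record in the MEDAL web application complements the questionnaire.

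Table 2 lists, under Lesson 1, "Educational video on energy density and portion sizes".

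On timing, the Phase 2 data collection section places baseline before the intervention and states that afterwards "students completed the post-intervention main questionnaire (consisting of the same questions as in pre-intervention"). Phase 3 data collection is described as similar, "with the addition of a mid-intervention, a 6-month post-intervention data collection". Lesson 1 therefore falls between baseline and the post-intervention wave.

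The Phase 3 data analysis section states: "Pre-post intervention comparisons of the behavioural outcomes will be assessed using appropriate statistical analyses", naming the paired t-test and the Wilcoxon signed rank test as examples. The first potential-effectiveness criterion in Table 3 is "Improvements in fruit and vegetable intakes", with no minimum size. The Phase 3 feasibility section adds that changes in behavioural outcomes are explored "to inform the decision-making of the primary outcome and power calculation for a subsequent larger definitive trial".

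**The concern.** A pre-post comparison assumes that the same eating would be reported in the same way at both times. Here the intervention includes teaching on portion sizes, and portion size is something the student supplies. If the lesson alters how a student judges a usual portion, servings per day can rise or fall while intake stays the same.

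Two uses of the result are at stake. The Table 3 criterion asks only for an improvement, so a small shift in judgement could meet it or hide a real gain. The observed change also feeds the choice of primary outcome and the power calculation for the definitive trial.

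This differs from the limitation stated in the Discussion, which is that a design without a control group cannot show what would have happened without the intervention. A control arm answers that problem. It would not by itself answer this one, because controls who did not receive Lesson 1 would not share any change in portion judgement.

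**Working it through.** **Sample size.** The article's only relevant figure is the target of 385, from a 95% confidence interval, a margin of 0.05 and an expected completion rate of 50%: n = 1.96² × 0.5 × 0.5 / 0.05² = 384.15, rounded up to 385. It reproduces. It concerns a completion rate and says nothing about servings; it is used below only as n. As a lower value I take 50% of 385 = 192.5, rounded up to 193.

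**Assumed inputs.** The article gives no baseline servings, no standard deviation (SD) of change and no size of any shift in judgement. I assume a baseline of 1 to 3 servings per day, an SD of change of 1.0 to 2.0, and a shift r in reported portion of 10% to 20% in either direction.

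**Shift in the mean.** Servings = frequency × portion. If eating is unchanged and every reported portion is multiplied by (1 + r), the mean moves by r × baseline:
- smallest: 0.10 × 1 = 0.1 servings per day
- largest: 0.20 × 3 = 0.6 servings per day

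**Smallest significant change** (two-sided 5%, paired test) = 1.96 × SD/√n:
- n = 385: 0.10, 0.15 and 0.20 for SD 1.0, 1.5 and 2.0
- n = 193: 0.14, 0.21 and 0.28

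**Chance that a pure shift in judgement is significant** = Φ(|shift| / (SD/√n) − 1.96), shown for SD 1.0 / 1.5 / 2.0:

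| Shift | n = 193 | n = 385 |
|---|---|---|
| 0.1 | 0.28 / 0.15 / 0.10 | 0.50 / 0.26 / 0.16 |
| 0.2 | 0.79 / 0.46 / 0.28 | 0.98 / 0.74 / 0.50 |
| 0.4 | >0.99 / 0.96 / 0.79 | >0.99 / >0.99 / 0.98 |
| 0.6 | >0.99 / >0.99 / 0.99 | >0.99 / >0.99 / >0.99 |

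A downward shift has the same chance of appearing as a significant decline. Table 3 does not require significance. If the criterion is read as any positive mean change, a smaller shift would be enough.

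**A case at fixed frequency.** Take 1.5 occasions per day and a portion of 1.0 before, with SD 1.5 and n = 385, so that the standard error is 1.5/√385 = 0.0764:
- portion 1.1 after: 1.5 × 0.1 = +0.15, z = 0.15/0.0764 = 1.96 (borderline)
- portion 1.25 after: 1.5 × 0.25 = +0.375, z = 4.9
- portion 0.8 after: 1.5 × (−0.2) = −0.30, z = −3.9

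**What the items already collected can show.** With F for frequency and P for portion, before (0) and after (1), each student's change splits exactly:

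F₁P₁ − F₀P₀ = (F₁ − F₀)P₀ + F₁(P₁ − P₀)

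The first term is the change with baseline portion held fixed; the second passes through the portion item. In the case with portion 1.1, the first term is 0 and the second is 0.15. A student who really ate portions 10% larger at the same frequency would give the same two numbers. The split shows how far the result depends on the portion item, not whether that part is real.

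**The case against.** The strongest reply is that the mechanism is plausible but not documented.

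- **The instrument is not shown.** Pictures, household measures or a serving definition printed at every wave would anchor the answer and largely remove the problem. The article says diet response options were modified after Phase 2, and an article may leave such detail to the full protocol.
- **The lesson content is not shown.** Lesson 1 is about calorie balance and nutrient density. Nothing says that it teaches fruit or vegetable servings.
- **MEDAL may help.** The article does not say whether the 3-day record depends on the same portion judgement.
- **Reliance is already limited.** The Discussion urges caution on effectiveness findings, and this is one of six potential-effectiveness criteria, alongside qualitative data.
- **The figures are illustrative.** Every input on servings is assumed. The calculation treats pairs as independent although students come from two schools; clustering would lower the probabilities, though it would leave the bias in place.

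Most of this stands, and it limits the claim to what may happen. It does not remove the point. The Discussion's caution concerns the missing comparison, not a change in the measure. Table 3 does ask whether the outcome measures are suitable and able to detect change, but its only stated criterion for the scales themselves is that they be appropriate and free of a ceiling effect. No check on changed portion judgement is described. MEDAL is a partial cross-check: students complete it too, and its dietary validation was against self-report.

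A reader might also infer that the criterion should be judged on frequency alone. The documents do not support that. Portion size is part of intake, and the canteen cues in Component D could plausibly act through larger portions. Frequency is itself self-reported by taught students, and changing the criterion's measure with analysis under way would be a post hoc change.

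**Conclusion.** The point holds as a possible measurement bias of unknown size and direction. The article establishes self-reported portion size, teaching on portion sizes between the measurements, and a within-student comparison. It follows that a change in servings per day, taken alone, cannot be read with confidence as a change in eating.

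Under the assumed ranges, a 10% to 20% shift in judgement moves the mean by 0.1 to 0.6 servings per day, against a just-significant change of 0.10 to 0.20 at n = 385. At the low end the effect is borderline or undetectable; at the high end it would almost certainly be significant. Firm anchoring of the portion item would make it much smaller.

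A reader might infer that the lesson does alter the measure, that any improvement would be an artefact, or that the definitive trial is bound to carry the error. The documents support none of these. Neither the portion item nor the lesson's fruit and vegetable content is shown, and the definitive trial's primary outcome has not been chosen.

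**What to change.** Keep servings per day as the measure for the Table 3 criterion. In the Phase 3 data analysis, add two supplementary results from items already collected:

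1. the pre-post change in frequency alone;
2. the pre-post change in servings with each student's baseline portion size held fixed, computed student by student.

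State the reading rule with them: if the improvement appears only through the portion item, it is not taken as evidence of increased intake unless frequency or the MEDAL record supports it. Show both versions of the servings change when informing the primary outcome and power of the definitive trial. The report should also say how the portion item was anchored, since that decides how much weight the point deserves.

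The cost is a little extra analysis and no new data. The drawback is that a genuine increase in portion size at constant frequency would be flagged as uncertain, because the split cannot by itself separate real from perceived portion change.

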#### Setting and participants

The setting, selection of schools, and participants for this pilot study followed the same procedures as Phase 2. However, two other schools were approached to participate in this study. The ideal number of participants for this phase was 385 students, following the same calculation in Phase 2.

Based on the feedback from Phase 2, more time was needed to complete the series of health education lessons in addition to the scheduled physical and health education lessons. Therefore, the schools in this pilot study were given 12 weeks to complete all the lessons and activities. Like Phase 2, consent was obtained from teachers for delivering the intervention and parents regarding data collection from their children. Students whose parents or guardians did not provide consent for data collection were allowed to attend the lesson without any data collected from them.

